**3.7.3. Randomisation**

The sequence numbers 1 to 500 will be allocated, with equal probability, to Vitamin D treatment and placebo treatment by a block random number generator (R Vienna Austria). Labelled bottles with the appropriate contents will be arranged in numerical order and the one with the lowest number among those unallocated will be used for the next recruited participant. Only the study statistician will have access to the randomisation codes and he will also be responsible for organising the preparation of the study treatment in conjunction with the Christchurch Hospital pharmacy dispensary. No research personnel that will have contact with the study participants will be involved in the preparation of the treatment, thus ensuring that those running the trial and the study participants remain blind to allocation.

**3.7.4. Follow-up**

At 6 weeks (± 1 week) post-study treatment all participants will be required to undergo a chest x-ray and provide a further blood sample for plasma calcium and serum 25OHD measures. Any women of reproductive age who thinks/knows they have become pregnant within the 6-week follow-up period will be excluded from further participation in the study and will not have a chest x-ray at 6 weeks. All participants will also be contacted by research staff at 6 weeks post-study treatment to answer a questionnaire regarding the resolution of symptoms and the return to normal activity.

Clinical data including length of hospital stay, in-hospital mortality rates, mortality rates at 6 weeks post-study treatment, intensive care admission rates, amount and duration of antimicrobial therapy and rates of relapse and readmission to hospital will be obtained from patient hospital records at 6 weeks post-study treatment. Twelve-month mortality rates will be obtained from national databases. This data will be analysed and reported subsequently to that of the 6 week follow-up data so the analysis and publication of the primary study findings is not delayed.

**3.7.5. Laboratory Procedures**

All laboratory procedures will be performed at Canterbury Health Laboratories under the supervision of [name].

**3.7.6. Training of Study Staff**

Training and education sessions for study personnel will be conducted in the month prior to the recruitment start date. The training will cover all study procedures, including recruitment and consenting as well as interviewing methods.

**3.7.7. Trial Registration**

The trial has been registered with the Australian and New Zealand Clinical Trials Registry; ACTRN12613000582752; http://www.ANZCTR.org.au

**3.7.8. Definition of the End of the Trial**

The end of the trial is the 6 week (± 1 week) post-study treatment follow-up chest x-ray and questionnaire completion regarding the resolution of symptoms and return to normal activity of the last participant.

**3.7.9. Discontinuation/Withdrawal of Participants from the Study**

Each participant has the right to withdraw from the study at any time. In addition, the investigator may discontinue a participant from the study at any time if the investigator considers it necessary for any reason including:

- Ineligibility (either arising during the study or retrospective having been overlooked at screening)
- Significant protocol deviation
- Significant non-compliance with study requirements
- An adverse event which results in inability to continue to comply with study procedures
- Corrected plasma calcium levels >2.6 mmol/L (see safety below)
- Disease progression which results in inability to continue to comply with study procedures
- Consent withdrawn
- Lost to follow up

The reason for withdrawal will be recorded. If the participant is withdrawn due to an adverse event, the investigator will arrange for follow-up visits or telephone calls until the adverse event has resolved or stabilised.

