**5.2. Statistical Analysis**

All randomised participants will be included in the primary analysis. Data will be analysed on an intention to treat basis with dropout events reported on and examined for differential compliance between treatment and placebo arms. Primary analysis will be logistic regression of clear chest X-ray on treatment arm with covariates for age (grouped) and gender and if appropriate severity and comorbidities. Additional analyses will include covariates for initial 25OHD level and 25OHD level during the study and stratified analyses by 25OHD level at baseline; deficient (<25nm/l) and insufficient (<50nm/L). All data will be analysed in R (Vienna, Austria) or SAS (NC,USA).

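### Section 3.7.9 lets investigators end follow-up of randomised participants who could still give the 6-week outcome, and this is not reconciled with the intention-to-treat analysis in Section 5.2

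*Protocol*

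**What the plan says.** Section 3.7.9 provides that "the investigator may discontinue a participant from the study at any time if the investigator considers it necessary for any reason including" eight listed grounds. Four matter here:

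- "Ineligibility (either arising during the study or retrospective having been overlooked at screening")
- "Significant protocol deviation"
- "Significant non-compliance with study requirements"
- "Corrected plasma calcium levels >2.6 mmol/L (see safety below")

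Two other grounds, adverse events and disease progression, apply only when the participant can no longer comply with study procedures. The four above carry no such limit. The section provides for contact after withdrawal in one case only, and only until the event settles: "If the participant is withdrawn due to an adverse event, the investigator will arrange for follow-up visits or telephone calls until the adverse event has".

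Sections 3.2 and 3.4 describe a single oral dose, given directly by research staff on enrolment. Under Sections 3.6.1 and 3.7.4 the primary outcome is a chest x-ray 6 weeks (± 1 week) after dosing. Section 3.7.4 adds that a woman who becomes pregnant during follow-up "will be excluded from further participation in the study and will not have a chest x-ray at 6 weeks".

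Section 5.2 states: "All randomised participants will be included in the primary analysis". The analysis is by intention to treat, and dropouts are to be reported and compared between arms.

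**The concern.** In a trial with continuing treatment, discontinuation can mean stopping the drug while follow-up goes on. Here the whole treatment has been given by the time the rule can operate, so discontinuation from the study means the end of study visits and contacts: the 6-week x-ray, blood sample and questionnaire.

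Three of the four grounds (later ineligibility, deviation, non-compliance) are ones for which an intention-to-treat analysis would normally keep the participant. The fourth, raised calcium, may be influenced by the study drug. Section 3.6.2 has calcium measured in real time to check for hypercalcaemia, and makes corrected calcium available to investigators before follow-up ends. Loss on that ground could therefore differ between arms even though investigators are blind to allocation.

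At stake is the completeness of the primary outcome. An analysis plan can say how missing x-rays are handled, but it cannot recover x-rays that the protocol allowed not to be taken.

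**Working it through.** **1. The passages side by side**

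| Question | Section | Answer |
|---|---|---|
| What is discontinued? | 3.7.9 | Participation in the study |
| Is treatment still to be given? | 3.2, 3.4 | No, one staff-given dose |
| Must the participant be unable to continue? | 3.7.9 | Only for adverse events and progression |
| How is the primary outcome obtained? | 3.6.1, 3.7.4 | X-ray at 6 weeks |
| Who is in the primary analysis? | 5.2 | All randomised |
| Does outcome collection continue after discontinuation? | none | Not stated |
| Is there a calcium rule in the safety section? | 4 to 4.4 | No |

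Sections 3.7.9 and 5.2 can both be followed to the letter, but the primary outcome of a discontinued participant may then not exist.

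**2. Is power at risk?** Inputs from Section 5.1: 50% versus 70% clear x-rays, 80% retention, uncorrected chi-square, power 0.8, 180 per arm. Alpha is not given there; I assume 0.05 two-sided.

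Evaluable n per arm = [1.96·√(2·0.6·0.4) + 0.8416·√(0.25 + 0.21)]² / 0.2² = (1.358 + 0.571)² / 0.04 ≈ 93. Recruited n = 93/0.8 = 116.25, so 117.

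The stated 180 per arm is therefore not reproduced, but this point does not rest on it. Taking 180 as given:

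- 80% retention, 144 evaluable: z = (0.2·√144 − 1.358)/0.678 = 1.54, power 0.94
- 60% retention, 108 evaluable: z = (0.2·√108 − 1.358)/0.678 = 1.06, power 0.86

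Extra withdrawals would not bring power below the target unless they were very numerous. The issue is bias.

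**3. How large could the bias be?** The documents give no withdrawal rates. Assume raised calcium removes 3% to 5% of the active arm and 1% of placebo:

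- Excess loss = 180·0.03 − 180·0.01 = 3.6, up to 180·0.05 − 180·0.01 = 7.2 participants

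Take a true 50% in both arms, 144 evaluable per arm (72 clear), and the extreme case that everyone lost in excess is unresolved:

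- 72/(144 − 3.6) = 72/140.4 = 51.3%, a shift of 1.3 points
- 72/(144 − 7.2) = 72/136.8 = 52.6%, a shift of 2.6 points

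**4. Sensitivity.** Same null setting, with m unresolved participants removed from one arm only. The rejection rate uses the pooled standard error for the test and the unpooled one for the sampling distribution.

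| m | Share of 180 | Clear in that arm | False difference | Rejection rate (nominal 0.05) |
|---|---|---|---|---|
| 5 | 2.8% | 72/139 = 51.8% | 1.8 points | 0.06 |
| 9 | 5.0% | 72/135 = 53.3% | 3.3 points | 0.09 |
| 18 | 10.0% | 72/126 = 57.1% | 7.1 points | 0.22 |

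These are worst cases: all removals fall in one arm and all have the same outcome.

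**The case against.** The case for leaving the text alone is substantial, and most of it limits the size of the problem.

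- **Participation is not analysis.** Section 3.7.9 does not say that discontinued participants leave the analysis or that collected data are discarded. Section 5.2 foresees dropouts, and Section 5.1 allows for 20% loss. This stands: a reader might infer a direct contradiction of intention to treat, but the text supports only an unreconciled conflict in practice.
- **Other outcomes survive.** Sections 3.6.3 and 3.7.4 take length of stay, intensive care, antimicrobials, readmission and 6-week mortality from hospital records, and 12-month mortality from national databases. This stands: it would be wrong to say that the rule deletes all outcomes.
- **Calcium timing.** Section 3.7.2 screens out hypercalcaemia before randomisation. Under Sections 3.6.2 and 3.7.4 the only scheduled post-dose sample falls at the 6-week follow-up, so a raised result would usually arrive when the x-ray is done or due. Section 3.4 also reports no hypercalcaemia in the cited single-dose studies. This stands, and makes the 3% to 5% assumption possibly high.
- **Safety follow-up.** A reader might infer that it is cut short. Section 4.2 counts abnormal test findings as adverse events, and Sections 3.7.9, 4.1 and 4.3 provide for following adverse events after withdrawal or until they settle. The documents do not support that inference.
- **Blinding.** Staff in contact with participants are blind (Section 3.7.3), and 25OHD results are withheld during follow-up (Section 3.6.2). The other three grounds have no evident route to unequal removal. This stands.

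What the objection does not meet is that the protocol permits loss of the x-ray and questionnaire in people able and willing to provide them, and says nowhere that collection continues.

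**Conclusion.** The point holds as a modest design fault that is cheap to repair. Section 3.7.9 permits avoidable loss of the primary outcome on grounds that do not prevent its collection, and it is not reconciled with Section 5.2. Raised calcium is the ground with a possible link to treatment, and its pointer to the safety section leads to no calcium rule.

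The illustrated size is 1.3 to 2.6 percentage points. It rests on assumed withdrawal rates that the documents do not supply, on every excess loss being unresolved, and on 144 evaluable per arm at a true 50%. A reader might take the excess losses as a share of 180 (3.6/180 to 7.2/180, or 2 to 4 points) as the shift in the result. That ratio is the extra fraction missing, not the change in the difference. Nor do the documents support saying that the randomised comparison is broken: the calcium schedule and the blinding make large unequal loss unlikely.

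**What to change.** In Section 3.7.9, state that participants discontinued for later-found ineligibility, deviation, non-compliance or raised calcium remain in outcome collection unless they withdraw consent. That covers the 6-week x-ray where it can be done, the questionnaire, hospital records and vital status. State also that data collected are kept and analysed as randomised, in line with Section 5.2.

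In Section 3.7.4, state that participants who do not have the x-ray still contribute the questionnaire and record-based outcomes.

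Reconcile the calcium ground's cross-reference with Section 4.

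A rule that only death or withdrawn consent can end follow-up is not needed. The grounds that already depend on inability to comply can stand. The change concerns data collection only and leaves the clinical handling of raised calcium and pregnancy untouched. It costs wording in two sections, one repaired cross-reference, and a few follow-up contacts that are already planned for every participant. The sample size does not change.

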**4. SAFETY**

Vitamin D intoxication, which is potentially fatal, is very rare, but can be caused by the ingestion of very high doses. The reported instances have been usually associated with prolonged intakes of more than 40,000 IU per day^93^. Although current data support the viewpoint that serum 25OHD levels must rise above 750 nmol/L to produce vitamin D toxicity, an upper limit of 250 nmol/L is used to ensure a wide safety margin^94^. Prolonged, continued oral intake in excess of 10,000 IU per day is required to produce a serum 25OHD of ≥250 nmol/L. A single high dose bolus of either 100,000, 300,000 or 500,000 IU vitamin D_3_ has been shown to be safe and effective in raising 25OHD levels in both healthy adults and elderly patients, with no reported incidences of intoxication^38,39,91^.

**4.1. Adverse Event Reporting**

Safety of exposure to vitamin D will be evaluated by the incidence of adverse events (AEs) and serious adverse events (SAEs), which will be reported in tabular form giving absolute numbers and percentages. Clinical oversight will be provided by investigators [name] and [name]. They will be responsible for assessing causality and whether the AE meets the criteria for an SAE. Each AE and SAE will be classified using the Common Terminology Criteria for Adverse Events (version 4.02; US department of Health and Human Sciences). All observed or volunteered AEs regardless of treatment group or suspected causal relationship to the investigational product will be reported as described in the following sections.

For all AEs, the investigators must pursue and obtain information adequate both to determine the outcome of the AE and to assess whether it meets the criteria for classification as a SAE requiring immediate notification to the designated representative. For all AEs, sufficient information should be obtained by the investigator to determine the causality of the AE. For AEs with a causal relationship to the investigational product, follow-up by the investigator is required until the event or its sequelae resolve or stabilize at a level acceptable to the investigator.

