**3.6.2. Blood Tests**

Blood samples will be collected at recruitment and at 6 weeks (± 1 week) after receiving study treatment and will be stored. Vitamin D (25OHD) levels will be measured on baseline blood samples at the end of the 6 week follow-up period to assess the proportion of people recruited into the study with deficient levels (<25 nmol/L). These baseline measures will be fed-back to the participant’s GP who will be responsible for the on-going care of the participant. The final blood sample collected at the end of the 6 week post- study treatment follow-up period will be stored and 25OHD levels measured after all participants have completed the 6 week follow-up period so as not to compromise the blinding of participants or research personnel. Plasma calcium and albumin levels will be measured in real-time on all samples collected and the corrected plasma calcium (i.e. corrected for plasma albumin concentration, as is standard laboratory practice) will be reported in order to check for hypercalcaemia (an elevated plasma corrected calcium is > 2.6 mmol/L). Only the corrected plasma calcium levels will be made available to investigators before the end of the 6 week follow-up period.

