**3.6.3. Assessment of Patient Outcomes**

Clinical data including basic demographics, routine haematological and biochemical information, length of hospital stay, in-hospital mortality, intensive care admission rates, amount and duration of antimicrobial therapy and rates of relapse and readmission to hospital and mortality rates at 6 weeks post-study treatment will be obtained from patient hospital records. For all participants, a CURB65 pneumonia severity score will be calculated from the clinical data collected. Research staff will also conduct a telephone interview with study participants at 6 weeks post-study treatment to complete a questionnaire regarding the resolution of symptoms and if the participants have returned to normal activity. Twelve-month mortality rates will be obtained from national databases.

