Disability is defined as a substantial disruption in a person’s ability to conduct normal life functions.

The relationship of the AE to Study Medication will be specified as follows:

1. Not related. In the investigators opinion, there is not a causal relationship between study medication and the AE.
2. Unlikely. Study medication is not likely to have any reasonable association with the AE.
3. Possibly. The AE could have been produced by the participant’s clinical state or study medication.
4. Probably. The AE follows a reasonable temporal sequence from the time of study medication administration and cannot be reasonably explained by the known characteristics of the clinical state.
5. Definitely. The AE follows a reasonable temporal sequence from the time of study medication administration.

AEs will be collected from the time of study drug administration through the follow-up period at 6 weeks post-study treatment. The investigators should attempt, if possible, to establish a diagnosis based on the presenting signs and symptoms. In such cases the diagnosis should be documented as the AE and not the individual sign/symptom. If a clear diagnosis cannot be established, each sign and symptom must be recorded individually.

The investigators should attempt to follow all unresolved AEs and/or SAEs observed during the study until they are resolved or judged medically stable, or are otherwise medically explained. If there is any doubt about whether the information constitutes a SAE, the information is treated as a SAE.

Certain information, although not considered an SAE, must also be recorded, reported, and followed up as indicated for an SAE. This includes:

- Overdose of an investigational product as specified in this protocol with or without an AE.
- Inadvertent or accidental exposure with or without an AE.

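### After discharge, no active enquiry is stated for non-serious adverse events or for serious events that do not lead to admission, although AE incidence is the safety measure

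*Protocol*

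**What the plan says.** Section 4.1 sets the safety measure: "Safety of exposure to vitamin D will be evaluated by the incidence of adverse events (AEs) and serious adverse events (SAEs"), tabulated as numbers and percentages. The same section states which events enter: "All observed or volunteered AEs regardless of treatment group or suspected causal relationship to the investigational product will be reported". Section 4.3 fixes the period: "AEs will be collected from the time of study drug administration through the follow-up period at 6 weeks post-study treatment".

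The planned contacts and data sources after discharge are these:

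- **Telephone interview at 6 weeks.** Research staff contact every participant "to answer a questionnaire regarding the resolution of symptoms and the return to normal activity" (section 3.7.4). Section 3.6.3 describes the same content, and so does the definition of the end of the trial in section 3.7.8.
- **Attendance at 6 weeks (± 1 week).** Under section 3.7.4, "all participants will be required to undergo a chest x-ray and provide a further blood sample for plasma calcium and serum 25OHD measures". Section 3.6.2 adds that "Plasma calcium and albumin levels will be measured in real-time on all samples collected", in order to detect hypercalcaemia.
- **Hospital-record review.** Section 3.7.4 covers deaths, intensive care admission and antimicrobial therapy, and "rates of relapse and readmission to hospital will be obtained from patient hospital records at 6 weeks post-study treatment".

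Section 4.2 makes investigators responsible for documenting every AE but gives no method of finding them.

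**The concern.** An incidence is only as complete as the method that finds the events. The stated rule relies on staff noticing an event or the participant mentioning it. In hospital that works reasonably well, because the participant is under daily care. At home, nobody from the study is due to ask anything until week 6, and the protocol does not say that anyone then asks about new health problems.

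At stake is the completeness of the AE table. If events managed by a GP, in an emergency department without admission, or by the participant alone go unrecorded, the reported incidence is too low. A real but modest harm of the bolus is then harder to see. The effect also reaches monitoring: under section 4.4 the 24-hour notice of an SAE to the committee runs from the investigators' awareness, which passive intake can delay or prevent.

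The protocol recognises this problem elsewhere. Section 2.3.4 criticises an earlier supplementation trial in post-menopausal women for under-estimating symptom prevalence because of the way the data were gathered.

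**Working it through.** No figure in the protocol is at issue, so there is none to reproduce. The check has two parts.

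**1. Which post-discharge events have a stated means of detection?**

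| Event after discharge | Looked for in every participant? | Source |
| --- | --- | --- |
| Death, intensive care admission, readmission, relapse | Yes, by record review | 3.6.3, 3.7.4 |
| Raised corrected calcium at week 6 | Yes, by blood test | 3.6.2, 3.7.4 |
| Persisting pneumonia symptoms | Partly, by questionnaire | 3.6.3, 3.7.4 |
| Other non-serious AE treated by a GP or self-managed | No means stated | – |
| Serious event without admission | No means stated | – |

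The last row is not empty in practice. Section 4.3 allows important medical events to be serious without hospitalisation. Its examples include bronchospasm needing intensive treatment at home or in an emergency room, and convulsions that do not lead to admission. The gap therefore extends beyond minor events.

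Two further points follow from the text:

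- The record review is specified as a source of outcome data. Death and hospitalisation are SAE criteria in section 4.3, yet no sentence says that what the review finds is passed into AE and SAE reporting.
- The calcium test after dosing is a single measurement at week 6. Section 2.2.4 puts the 25OHD peak after a D3 bolus at 7 to 14 days, a period with no scheduled post-discharge contact. Symptoms arising at home in that period are recorded only if the participant brings them up.

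**2. How much of the AE window lies after discharge?**

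Share after discharge = (window − days in hospital after the dose) / window. The window is 42 days, or 35 to 49 with the ± 1 week allowance. The protocol gives no length of stay, so 3 to 14 days is an assumption.

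- 3 days: (42 − 3)/42 = 93%
- 5 days: (42 − 5)/42 = 88%
- 7 days: (42 − 7)/42 = 83%
- 10 days: (42 − 10)/42 = 76%
- 14 days: (42 − 14)/42 = 67%

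For the same 3 to 14 days, a 35-day window gives 91% to 60% and a 49-day window gives 94% to 71%. Across this range most of the window falls after discharge. These are shares of time, not of events. AEs in acute pneumonia may well cluster early, so the share of events exposed to the gap could be smaller.

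**The case against.** The strongest reply is that safety ascertainment is more systematic than the wording of section 4.1 suggests. Records are reviewed for the gravest outcomes, calcium is checked at week 6, there is an attendance as well as a telephone call, and a symptom questionnaire is partial elicitation, since section 4.2 counts clinically significant symptoms as AEs. Findings from these sources can reasonably be called observed. The questionnaire is a separate document approved by the ethics committee (section 7.1) and is not shown, so an open health question may already be in it. AE prompts are also often left to case report forms.

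Most of this stands, and it limits the point to the last two rows of the table. It does not remove it. Section 4.1 states an intake rule, and that rule omits elicited events. The interview is described three times without any AE enquiry. The duty in section 4.1 to pursue information begins only once an AE is known. If the questionnaire already contains an open question, the amendment simply records it.

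A reader might infer three stronger things that the documents do not support:

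- **That 6-week safety data as a whole rest on chance reporting.** The record review and the calcium test rule this out.
- **That the arms are compared unfairly if vitamin D shortens the stay.** All participants are observed to 6 weeks (section 3.5) and the trial is double blind. Only the intensity of detection could differ, and only if treatment changes length of stay.
- **That a stated amount of power to detect harm is lost.** AEs are to be tabulated, with no hypothesis test planned, and the protocol gives neither AE risks nor capture rates from which to calculate it.

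**Conclusion.** The point holds as a cheap improvement. Non-serious AEs, and serious events that do not lead to admission, have no stated active ascertainment between discharge and week 6 or at the week-6 contacts. The likely consequence is under-counting, probably similar in both arms because of blinding, with some loss of sensitivity to harm. Bias between arms is not the main worry.

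The number of events lost cannot be derived from the protocol. The only size available is the exposed time: roughly two thirds to nine tenths of a 42-day window, resting on the assumed 3 to 14 days in hospital after the dose. The conclusion also rests on the protocol's description of the questionnaire, whose items are not shown.

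**What to change.** Make three changes to the text:

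1. In section 4.1, widen the intake rule to AEs that are observed, volunteered or elicited.
2. In section 3.7.4, add to the existing 6-week telephone interview one fixed, open AE question, asked identically of every participant while participant and staff are blinded: any new or worsened health problem since the study dose, with its date and any GP or emergency contact.
3. State that events found in the 6-week hospital-record review that meet the AE or SAE definitions are entered as such.

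The cost is a few minutes per interview and more non-serious AEs to code. No new visit or procedure is needed, and no treatment rule changes.
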